### Randomisation

Randomisation takes place at the OP level, because workers cannot be randomly allocated to an OP in the intervention group or an OP in the control group since every OP is allied to a specific company. All participating OPs are randomised by computerised allocation to the intervention group or control group at OHS agency level.

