**Methods/design:**

This is a two-armed cluster-randomised controlled trial with randomisation at the occupational physician level. During one year, occupational physicians in the intervention group receive innovative training to improve their guideline-based care whereas occupational physicians in the control group provide care as usual. A total of 232 workers, sick listed due to common mental disorders and counselled by participating occupational physicians, will be included. Data are collected via the registration system of the occupational health service, and by questionnaires at baseline and at 3, 6 and 12 months. The primary outcome is time to full return-to-work. Secondary outcomes are partial return-to-work, total number of sick leave days, symptoms, and workability. Personal and work characteristics are the prognostic measures. Additional measures are coping, self-efficacy, remoralization, personal experiences, satisfaction with consultations with the occupational physician and with contact with the supervisor, experiences and behaviour of the supervisor, and the extent of guideline adherence.

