### Study design

The study is designed as a two-armed cluster RCT with randomisation at the OP level (Figure 1). All participating OPs are recruited from a large collaborating OHS in the Netherlands. The OPs are randomised to an intervention group or a control group. Using an innovative training, OPs in the intervention group are trained to counsel sick-listed workers according to the Dutch national guideline ‘Management of mental health problems of workers by occupational physicians’. OPs in the control group receive no training and counsel sick-listed workers with care as usual. Workers are invited by the OHS after their first meeting with the OP. Data on sick leave and RTW of all invited workers are anonymously extracted from the registration system of the OHS during 1-year follow-up. In addition, in case of consent the worker receives a questionnaire at baseline (T0), and at 3 months (T1), 6 months (T2) and 12 months (T3) post baseline. In addition, 2 months after baseline a short questionnaire is sent to their supervisor.

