#### Content of the training

OPs participating in the study and allocated to the intervention group received training in the guideline before the start of the study. This training was specifically designed for the purpose of this study and consisted of 8 meetings within 12 months. Each meeting took 2 h and was provided in groups of 4-6 OPs under the guidance of a trainer. The aim of the training was to enhance guideline adherence of the participating OPs by focussing on barriers that prevent OPs from using the guideline and finding solutions to overcome these barriers. This is considered to be a successful strategy for the implementation of guidelines [15,16].

During the 8 meetings the (key) recommendations within each consecutive step of the guideline were discussed. These discussions first focussed on barriers that would hinder OPs from using the specific recommendation in practice. The analysis of barriers was structured and based on an existing framework of barriers [17]. According to this framework guideline adherence can be affected by three main categories: 1) knowledge-related barriers (lack of awareness and lack of familiarity), 2) attitude-related barriers (lack of agreement, lack of self-efficacy, lack of outcome expectancy and lack of motivation/inertia of previous practice) and 3) external barriers that hinder physicians to apply the guideline in practice (guideline factors, environmental factors and patient factors). Second, the OPs in the group were invited to suggest solutions to address the perceived barriers taking into account the context of their daily practice. Third, the OPs drew up an action plan of how to implement these solutions in their daily practice, and agreed on learning objectives and ‘homework’ assignments. Between the meetings (a period of about 6 weeks) the OPs practiced the suggested solutions to experience if and how these would help to apply the guideline recommendations. During the next meeting the experiences of the OPs were evaluated and, when necessary, the solutions were adjusted to what the OPs had experienced in practice. This cycle of plan-do-check-act was repeated in each meeting for all the recommendations stated in the guideline.

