### Statistical analysis

Survival analyses will be used to analyse the primary outcome (time to full RTW) and the time to partial RTW comparing the intervention and the control group, while taking into account the effect of clustering of workers within OPs. Longitudinal multilevel analysis will be used to analyse the secondary outcomes.

To detect significant differences in the baseline characteristics between the intervention group and control group descriptive analyses will be used. If necessary these differences will be taken into account in the effect evaluation.

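### OPs appear to be randomised within OHS agencies, but the stated analysis leaves the agency out, so its standard errors are slightly too wide

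*Protocol article*

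**What the plan says.** The unit of allocation is named several times in the protocol article:

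- Abstract, Methods/design: "This is a two-armed cluster-randomised controlled trial with randomisation at the occupational physician level".
- Study design: "The study is designed as a two-armed cluster RCT with randomisation at the OP level", followed by "The OPs are randomised to an intervention group or a control group".
- Randomisation, opening: "Randomisation takes place at the OP level".
- Randomisation, next sentence: "All participating OPs are randomised by computerised allocation to the intervention group or control group at OHS agency level".

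The agency's role in the allocation is not explained. Agencies otherwise appear only in Recruitment of OPs, where the study is said to have been presented at several of them, with no number given.

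For the primary outcome and time to partial return-to-work, Statistical analysis specifies survival analysis "while taking into account the effect of clustering of workers within OPs". The other secondary outcomes get a longitudinal multilevel analysis whose levels are not named. Agency is not mentioned there.

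Content of the training describes the intervention meetings: "Each meeting took 2 h and was provided in groups of 4-6 OPs under the guidance of a trainer". There were eight such meetings.

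**The concern.** Two consecutive sentences attach the word level to two different units, the OP and the agency. In a cluster trial the analysis should follow the allocation. The cluster must be the unit allocated, and a factor that constrained the allocation is normally carried in the model. If agency was a stratum, the stated analysis has the right cluster but leaves variation between agencies in the error term, although the design has already balanced it across arms. What is at stake is a modest loss of precision, and a sentence that a reader could take for a different design.

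**Working it through.** **1. Which unit does the sample size imply?** Inputs from Sample size: 55% vs 75% at 3 months, 75% vs 90% at 6 months, 80% power, alpha 0.05 (two-sided reproduces the figures), ICC 0.025, 5% attrition.

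- The pooled two-proportion formula without continuity correction gives 89 and 100 per arm before the cluster correction.
- The stated 97 and 110 imply design effects of 97/89 = 1.09 and 110/100 = 1.10.
- From DE = 1 + (m − 1) × 0.025, m = 1 + 0.09/0.025 = 4.6 and m = 1 + 0.10/0.025 = 5.
- Attrition: 2 × 110 / 0.95 = 231.6, i.e. 232, as stated.

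The plan's figures are therefore reproduced with about 4 to 5 workers per cluster. Strengths and limitations counts 60 OPs with 3 to 4 workers each (232/60 = 3.9), and 232 over the 66 recruited OPs is 3.5. Whole agencies would be larger: 232 workers over an assumed 6 to 20 agencies is 39 down to 12 each. Clusters of 5 would need 232/5, or about 46 units, which hardly fits several agencies. The sample size fits the OP as cluster.

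**2. Cost of leaving the stratum out.** Set the total variance of a worker's outcome to 1. Split the ICC of 0.025 into 0.01 between agencies (assumed) and 0.015 between OPs within agencies, leaving 0.975 between workers. With m workers per OP, the variance factor per worker is:

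- agency omitted: 0.975 + 0.025m
- agency included: 0.975 + 0.015m

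| m | omitted | included | SE ratio | SE reduction |
|---|---|---|---|---|
| 3.5 | 1.0625 | 1.0275 | √(1.0275/1.0625) = 0.983 | 1.7% |
| 20 | 1.475 | 1.275 | √(1.275/1.475) = 0.930 | 7.0% |

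The value m = 20 is an assumption. It is included because Recruitment of participants extracts absence data for every eligible worker, not only for questionnaire participants, so OP clusters could exceed 3 to 4. If no variance lies between agencies, the reduction is nil. At the boundary where all 0.025 does (so that OPs in one agency do not differ), it is 1 − √(0.975/1.0625) = 4.2% at m = 3.5 and 1 − √(0.975/1.475) = 18.7% at m = 20. These are linear-scale approximations to a survival model.

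**3. Direction of the error.** An OP-level test was simulated with an assumed 10 agencies × 6 OPs × 4 workers, an OP ICC of 0.025, and a further agency ICC of 0.01, 0.025 or 0.05. With OPs allocated within agencies and agency ignored, the type I error at nominal 0.05 was 0.047, 0.041 and 0.034. The test is conservative throughout.

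**4. Training groups.** Take groups of 5 OPs (the stated range is 4 to 6), 3.5 workers per OP, and a group ICC g forming part of the 0.025 (g assumed). The control-arm design effect is 1.0625. For the intervention arm it is 0.975 + 3.5 × (0.025 − g) + 17.5g, which is 1.20 at g = 0.01 and 1.41 at g = 0.025. The ratio of true to reported SE is √[(1.0625 + 1.20)/2.125] = 1.03 up to √[(1.0625 + 1.41)/2.125] = 1.08. This corresponds to a type I error of about 5.8% to 6.9%. The upper end is a boundary case in which OPs in one group do not differ at all.

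**The case against.** **The stronger reading.** A reader might infer that whole agencies were allocated, so that an OP-level analysis understates the error and the trial lacks its stated power. If that were so, the consequences would be real. With an assumed 6 to 20 agencies and an agency ICC of 0.005 to 0.025, 6-month power at 110 per arm runs from 0.82 down to 0.56. The simulation in step 3 gives type I errors of 0.069, 0.103 and 0.151. The documents do not support this reading. The abstract, Study design and the sentence just before the agency phrase all name the OP, and the sentence with the phrase itself makes OPs the objects randomised. The sample size is also built on OP-sized clusters. The 0.56 further needs the entire planned ICC to sit at agency level, with only six agencies.

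**The case for leaving the text alone.** This is a journal article; the full analysis plan is not shown and may carry agency as a stratification factor. The analysis paragraph is a summary and does not say that OP is the only level modelled. With the OP as the unit, OP clustering is valid, and the loss at the planned cluster size is under 2% on the working assumption. Much of this stands. It rules out any claim of invalid inference and makes the point small. What remains is that the article names the agency in the allocation, leaves its role unclear, and states an adjustment that omits it.

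**Training groups.** It can fairly be said that this is a separate matter, that its size rests wholly on assumed ICCs, and that a variable grouping OPs in one arm only would reveal allocation to the analyst, whom Blinding describes as blinded. All of that stands, so it warrants no more than an optional sensitivity analysis.

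**Conclusion.** The point holds in a limited form. The agency phrase most plausibly means that OPs were allocated within agencies, and the stated analysis leaves that stratum out. OP clustering matches the unit of allocation, so on this point the stated power is not undermined and the inference is not anti-conservative. The cost is precision: about 1.7% of the standard error at 3.5 workers per OP, or about 7% at 20 per OP, if 0.01 of the ICC of 0.025 lies between agencies. That split and the figure of 20 are assumptions, as the article gives neither the number of agencies nor an agency-level ICC. Correlation within training groups could act the other way (true SE 3 to 8% larger than reported at assumed group ICCs of 0.01 to 0.025), but the document gives no basis for sizing it.

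**What to change.** 1. Reword the Randomisation section so that the unit appears once: *OPs randomised within OHS agency*.
2. Stratify the primary survival model, and that for partial return-to-work, by agency. Include agency as a fixed effect in the multilevel models. Keep OP as the cluster throughout. If the full analysis plan already does this, only the rewording is needed.
3. If the sponsor confirms that whole agencies were in fact allocated, make agency the cluster and restate the power. Otherwise leave the sample size alone.
4. Optionally, once the blinded primary analysis is complete, add a sensitivity analysis that clusters intervention OPs by training group and treats each control OP as its own group.

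**Cost.** Steps 1 and 2 change wording and model specification only; no new data should be needed, since the sponsor should know each OP's agency. The price is a few degrees of freedom, depending on the number of agencies. An agency whose OPs all fell in one arm would add nothing to a stratified comparison. Step 4 reveals the arms to whoever runs it, so it must come after the primary result is fixed.

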### Blinding

Workers and companies are blinded for randomisation since they are not aware of the allocation of their OP. The researcher who performs the analyses ([name]) is blinded for allocation to intervention or care as usual.

### Statistical analysis

Survival analyses will be used to analyse the primary outcome (time to full RTW) and the time to partial RTW comparing the intervention and the control group, while taking into account the effect of clustering of workers within OPs. Longitudinal multilevel analysis will be used to analyse the secondary outcomes.

To detect significant differences in the baseline characteristics between the intervention group and control group descriptive analyses will be used. If necessary these differences will be taken into account in the effect evaluation.

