#### Prognostic measures

•Personal characteristics such as age, gender, level of education, sick leave in the previous year, history of mental disorders, and expectations about full RTW are measured at baseline.

•Work characteristics such as number of working hours, contract type, type of work, profession and job content are measured at baseline. Job content is measured with the Dutch version of the Job Content Questionnaire (JCQ) [25], a self-report questionnaire which measures the social and psychological characteristics of jobs. The JCQ assesses the following scales: psychological job demands, decision latitude, social support, physical demands and job insecurity.

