### Sample size

A power analysis was performed to determine the sample size needed to detect a difference between the control and intervention group with respect to the time workers fully return to their work (primary outcome measure). Proportions of full RTW were adopted from previous studies [7,30]. It was assumed that in the usual care (control) group 55% of the workers would have returned to work after 3 months and 75% after 6 months, whereas in the intervention group these figures would be 75% and 90%, respectively. With a power of 80% at a 0.05 alpha level, assuming an ICC of 0.025 and taking into account a correction factor for the clustered design, it was calculated that 2 × 97 workers would be needed to detect the difference after 3 months and 2 × 110 workers for the difference after 6 months. Allowing for 5% attrition on the sick leave data, a total of 232 workers need to be included.

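### Covariate adjustment is tied to significant baseline differences instead of a set of prognostic factors named in advance

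*Protocol article*

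**What the plan says.** The Statistical analysis section of the protocol article describes the primary analysis as a survival analysis "comparing the intervention and the control group, while taking into account the effect of clustering of workers within OPs". It names no covariate. Two sentences then deal with adjustment: "To detect significant differences in the baseline characteristics between the intervention group and control group descriptive analyses will be used", followed by "If necessary these differences will be taken into account in the effect evaluation". The differences in the second sentence are the ones that the first sets out to detect. The article does not say what would make adjustment necessary.

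The Prognostic measures section lists candidate predictors. The personal ones are age, gender, education and previous-year sick leave, and it adds that "history of mental disorders, and expectations about full RTW are measured at baseline". On the work side it states: "Work characteristics such as number of working hours, contract type, type of work, profession and job content are measured at baseline". Nothing links this list to the effect model.

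The Randomisation section says "All participating OPs are randomised by computerised allocation to the intervention group or control group at OHS agency level". Agency does not reappear in the analysis.

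**The concern.** A test of baseline balance measures how far apart the arms are relative to sampling error. It carries no information on whether the factor predicts time to RTW. If the arms differ only by chance, any factor, strong or weak, reaches p<0.05 in roughly one trial in twenty. A rule built on that test therefore leaves strong predictors out most of the time and occasionally lets in irrelevant ones.

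Three things are at stake:

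- **Power.** In a proportional hazards model, leaving out a strong predictor pulls the treatment HR towards 1 and costs power.
- **Uncorrected imbalance.** A difference in a strong predictor that falls short of significance is left in the estimate. Workers enter after their occupational physician (OP) has been randomised, so such differences can come from recruitment as well as from chance.
- **A data-dependent target.** The HR is non-collapsible: its value depends on which covariates are in the model. If the set is decided after seeing baseline data, so is the HR that the trial estimates.

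**Working it through.** **1. The plan's own sample size.** Inputs from the Sample size section: in the control arm "55% of the workers would have returned to work after 3 months and 75% after 6 months"; "in the intervention group these figures would be 75% and 90%, respectively"; power 80%, alpha 0.05 (taken as two-sided), ICC 0.025, 5% attrition. The Strengths and limitations section gives 60 OPs with 3-4 workers each.

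Two-proportion formula: n = [1.96·√(2p̄(1−p̄)) + 0.84·√(p₁(1−p₁)+p₂(1−p₂))]² / (p₁−p₂)². This gives 89 per arm (55% v 75%) and 100 per arm (75% v 90%).

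Design effect 1+(m−1)×0.025:
- m=4: 89×1.075 = 95.7, so 96; 100×1.075 = 107.5, so 108.
- m=5: 89×1.10 = 97.9; 100×1.10 = 110.0.

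The stated 97 and 110 lie in this range, and 220/0.95 = 231.6, so 232. The sample size reproduces without covariates, and this point does not touch it.

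**2. Effect size implied by the design.** Under proportional hazards, ln(0.25)/ln(0.45) = 1.74 at 3 months and ln(0.10)/ln(0.25) = 1.66 at 6 months.

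**3. What the rule does to power.** Simulation with 60 OPs, 232 workers, follow-up censored at 365 days, and a Cox model with OP-clustered robust standard errors; 2,000 runs per setting. The control hazard is −ln(0.45)/91 = 0.00877 per day, from the 3-month control proportion.

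Assumptions not in the documents: treatment HR 1.5 (log HR 0.405); one standardised prognostic covariate with intra-OP correlation 0.02; OP effect SD 0.1 on the log-hazard scale. Under the rule, the covariate enters only if its baseline p<0.05.

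| Covariate log HR per SD | Power, always adjusted | Power, rule | Power, unadjusted | Always adjusted minus rule |
|---|---|---|---|---|
| 0.3 | 83.2% | 78.1% | 77.6% | 5.1 points |
| 0.5 | 83.6% | 70.7% | 69.8% | 12.9 points |
| 0.8 | 83.4% | 58.2% | 56.0% | 25.2 points |

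The covariate was selected in 5.3% to 6.8% of runs, whatever its strength. The mean treatment log HR under the rule was 0.377, 0.345 and 0.302, against 0.402, 0.403 and 0.407 when always adjusted. With no treatment effect, rejection rates were 5.6%, 4.9% and 4.7% under the rule, and 5.7%, 5.8% and 5.9% always adjusted.

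The gap depends on the assumed treatment effect. A rough rescaling to HR 1.66 multiplies (1.96 + z_power) by ln 1.66/ln 1.5 = 1.25. For covariate log HR 0.8, the rule gives 2.167×1.25 = 2.71, power about 77%. Always adjusting gives 2.930×1.25 = 3.67, power about 96%. The gap is then about 18 points; the same step gives about 8 points at 0.5 and 3 points at 0.3.

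**4. Imbalance that the test misses.** With 232/2 = 116 workers per arm and clustering ignored, the largest non-significant difference is 1.96×√(2/116) = 0.257 SD. For an assumed covariate log HR of 0.4 per SD, the shift is 0.257×0.4 = 0.103, a factor of exp(0.103) = 1.11. Relative to the design effect, this is 0.103/ln 1.66 = 20%, or 0.103/ln 1.74 = 19%.

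**5. Chance of a spurious covariate.** For k independent tests at 0.05, the chance is 1−0.95^k: 19% for k=4, 30% for k=7 (the personal characteristics in Table 1), and 54% for k=15 (adding three work items and five job-content scales).

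**The case against.** The case for leaving the text alone has real force:

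- The second sentence is conditional and does not rule out weighing prognostic relevance. An article may leave the covariate list to a fuller plan.
- The Blinding section says that the analysing researcher does not know the allocation, which limits steering.
- Looking at balance has a legitimate purpose when workers are recruited after OPs are randomised.
- The power losses rest on assumed effects, and much of the lower HR reflects non-collapsibility, not bias.

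These points limit the concern but do not remove it. The article states a selection criterion, significance, and a later plan that follows it inherits the weakness. Blinding does not fix the set in advance. Recruitment-related imbalance is a reason to describe balance and to adjust regardless, because a test passes over everything below its threshold.

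Stronger readings do not hold:

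- A reader might infer that type I error is inflated or the confidence interval invalid. The simulation, with one covariate and the rule applied mechanically, shows no inflation.
- A reader might put the chance of a spurious covariate in the primary model at 54% to 79%. That needs 15 to 30 independent tests. Reaching 30 means counting symptom, burnout and coping scales that are unlikely to be independent. A registry-based model with about four candidates gives about 19%.
- A reader might take the factor of 1.11 as the expected bias. It is a boundary case, with the imbalance exactly at the threshold and an assumed covariate effect.

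**Conclusion.** The point stands as a weakness in a stated method. Adjustment hangs on observed significance and an undefined condition, so the listed prognostic measures would usually be left out and the choice made after seeing the baseline data.

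The main cost is power: about 5 to 25 points for a covariate log HR of 0.3 to 0.8 per SD at an assumed treatment HR of 1.5, and less if the true effect is nearer the 1.66 to 1.74 that the design implies. Sub-threshold imbalance and a data-dependent target HR come on top. The trial remains valid and its sample size reproduces. The change should be made before the analysis.

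**What to change.** Replace the two sentences in the Statistical analysis section:

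- Drop significance testing as the covariate selector and keep the baseline table descriptive.
- Name a short adjustment set from the Prognostic measures that is available for everyone in the primary analysis population, for example age, gender and sick leave in the previous year. Add OHS agency, the level at which the Randomisation section places the allocation.
- Put questionnaire-only covariates (education, history of mental disorders, RTW expectations) in the models for questionnaire responders.
- Apply the set whatever the observed balance, and report the unadjusted HR beside the adjusted one.

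The text change is small, but availability must be confirmed first. The Study design and Recruitment of participants sections promise only sick leave and RTW data for workers outside the questionnaire study, and Table 1 gives no registry source for age or gender. The number of agencies is not stated and affects how agency can enter the model. The adjusted HR will be conditional on the covariates, and the plan must say how missing covariate values are handled.
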